**Methods:**

This single-arm trial will enroll 20 parents with overweight or obesity of children (8-11 years) with overweight or obesity, both of whom are at risk for T2DM. Parents will meet in small groups (5 parents per group) weekly for 11 weeks and then monthly for 4 monthly maintenance sessions via videoconference using Wi-Fi–enabled iPads with cellular connectivity. The intervention will be adapted from the National Diabetes Prevention Program and *Power to Prevent*, a diabetes prevention program tailored for AA families. The same lifestyle intervention facilitated by a racially concordant lifestyle coach trained in the Diabetes Prevention Program will be delivered to all groups (n=4). Participants will be recruited in-person during patient encounters at the UMMC’s pediatric weight management clinic. Sessions will consist of dietary and physical activity behavior change strategies facilitated using problem-solving and goal-setting skills. The implementation strategy has 2 targets: the pediatric weight management clinic site and clinical team and parents of children at risk for T2DM engaged in intensive obesity treatment to prevent T2DM. The multifaceted implementation protocol includes 4 discrete strategies: creating a new clinical team, changing the service site, intervening with families, and promoting organizational readiness for change.

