### Objectives

The Telehealth Diabetes Prevention Intervention for the Next Generation of African American Youth (TELE-GEN) pilot trial proposes implementing and evaluating a diabetes prevention intervention based on the *Power to Prevent* program for AA parents of children (8-11 years) who are both overweight or obese and at risk for T2DM. Historically, a lengthy effectiveness study conducted under *ideal circumstances* would be the next step in identifying a gold standard lifestyle intervention to prevent T2DM in AA youth; however, standard effectiveness studies are limited by their inability for rapid translation and the need for subsequent implementation studies to validate utility in real-world settings [43]. Hybrid research designs leverage the rigor of clinical trials and implementation science to foster rapid translation and effective implementation [33,43]. Thus, in partnership with the Center for Telehealth at the University of Mississippi Medical Center (UMMC) and pediatric weight management clinic, we propose a novel effectiveness-implementation hybrid type II research design [43] with the coprimary aim to (1) conduct a 30-week, single-arm pilot trial with at-risk parents of at-risk children to assess the early efficacy of Power to Prevent delivered using small group-based videoconferencing to reduce BMI in parents (n=20) and stabilize or reduce BMI z scores in children (n=20), while (2) conducting a comprehensive evaluation of a multifaceted implementation strategy for the uptake of the intervention by the pediatric weight management clinic at the UMMC in Jackson, Mississippi. The protocol described below was approved by the UMMC’s Institutional Review Board (#2020V0249).

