The power calculation, across 5 scenarios, shows detectable effect sizes, ≥−2.5 (SD 0.05) BMI in parents [58] and in children, where a modest reduction in BMI z score (≥0 to <−0.1, SD 0.05) has been associated with improved cardiometabolic risk [59]. In the first 3 scenarios, assuming 10% attrition [37], a minimum of 18 dyads are needed. In scenarios 4 and 5, detectable effect sizes are reported in the case of 0% (n=20 dyads) and 20% (n=16 dyads) attrition. We anticipate 20% attrition, which is consistent with the group- and family-based telehealth lifestyle intervention literature [60-62]. Analyses are based on α=.05 and a conservative two-sided test. An effect size of 1.0 is considered substantial and 0.5 is considered medium. We will obtain reliable effect size estimates to design a pilot randomized controlled trial.

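### The stated minimum of 18 dyads assumes 10% attrition, but the plan anticipates 20%, which leaves 16 of the 20 enrolled; the n=16 scenario should be the base case

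*Protocol article*

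**What the plan says.** All the relevant statements are in the protocol article, and the main ones stand in one paragraph of Participant Recruitment and Sample Size.

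- **Enrolment.** The Abstract (Methods) and the Objectives fix it at 20 parents and 20 children, that is, 20 dyads.
- **Scenarios 1 to 3.** "assuming 10% attrition [37], a minimum of 18 dyads are needed".
- **Scenarios 4 and 5.** "detectable effect sizes are reported in the case of 0% (n=20 dyads) and 20% (n=16 dyads) attrition".
- **Forecast.** "We anticipate 20% attrition, which is consistent with the group- and family-based telehealth lifestyle intervention literature".
- **Test.** Alpha is 0.05, two-sided. Effect sizes of 0.5 and 1.0 are given as benchmarks for medium and substantial. No power is stated, and no detectable value is attached to any single scenario.

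**The concern.** The only sentence that says how many dyads are required rests on an attrition rate that the team does not expect. The rate it does expect appears as one of two alternative scenarios, after three scenarios built on the more favourable rate. A reader who takes the paragraph at face value learns that 18 dyads are required and that 16 are likely to remain, and is not told whether 16 is enough.

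The same paragraph says that the trial will give reliable effect-size estimates for designing a randomized pilot. The precision to quote for that purpose is the one at the expected number of dyads, not at a number reached only with better retention.

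**Working it through.** **Inputs from the document.** 20 dyads enrolled; attrition of 0%, 10% and 20%; a stated minimum of 18; 20% anticipated; alpha 0.05 two-sided.

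**Assumptions of this check.** Power of 80% or 90%, because none is stated; a one-sample t test on the within-person change; independent dropout for the probability in step 2.

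**Step 1: reproduce the plan's counts.** Retained = enrolled × (1 − attrition).

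- 0%: 20 × 1.00 = 20
- 10%: 20 × 0.90 = 18
- 20%: 20 × 0.80 = 16

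All three counts match the document. At the anticipated rate the shortfall against the stated minimum is 18 − 16 = 2 dyads, or 2/18 = 11%.

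The 18 reproduces only as 20 less 10%. It cannot be recovered as a power-based minimum, because power is missing. The printed effects and SDs do not lead to it either: 2.5/0.05 = 50 SD for parents and 0.1/0.05 = 2 SD at most for children, and an effect of 2 SD would need only 5 dyads.

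**Step 2: chance of retaining at least 18 of 20.** Binomial, P(X ≥ 18) = P(18) + P(19) + P(20).

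- Retention 0.80: 190 × 0.8^18 × 0.2^2 + 20 × 0.8^19 × 0.2 + 0.8^20 = 0.137 + 0.058 + 0.012 ≈ 0.206 (computed unrounded)
- Retention 0.90: the same terms give 0.285 + 0.270 + 0.122 = 0.677

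**Step 3: detectable standardized change.** Solve for d in P(|T| > t(0.975, n−1)) = power, where T is noncentral t with n − 1 degrees of freedom and noncentrality d√n.

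| Dyads | 80% power (assumed) | 90% power (assumed) |
|---|---|---|
| 20 | 0.66 SD | 0.76 SD |
| 18 | 0.70 SD | 0.81 SD |
| 16 | 0.75 SD | 0.87 SD |

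**Step 4: the same loss in power.** The change detectable with 80% power at 18 dyads (0.70 SD) has 74.5% power at 16. The change detectable with 90% power at 18 (0.81 SD) has 85.8% at 16.

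**Step 5: power at the plan's own benchmarks.** At 1.0 SD, power is 0.979 with 18 dyads and 0.962 with 16. At 0.5 SD, it is 0.516 and 0.465.

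**The case against.** The strongest defence is that the 18 is conditional. It belongs to scenarios 1 to 3 and their 10% assumption, and scenario 5 is exactly the anticipated case. The article prints no scenario-by-scenario results for any of the five, so the value for 16 dyads may well be in the full protocol, and its absence here is not a fault. With no stated power, no target can be shown to fail. In a detectable-effect calculation, fewer dyads mean only a somewhat larger detectable effect, and step 5 shows that neither benchmark changes its reading.

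Most of this stands, and it limits the point. It does not remove it. Listing a scenario with 16 dyads neither withdraws the sentence that calls 18 a minimum nor identifies 16 as the planning case. If 18 is simply 20 less 10%, then describing it as a requirement is wrong and still needs correcting. The intention-to-treat statement under Data Analysis does not help either, because the sample-size paragraph counts dyads remaining after attrition.

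Two stronger readings are tempting.

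- A reader might infer that the team overlooked 20% attrition or that the trial is shown to be underpowered. The document supports neither: it lists the 20% case and states no power to fall short of.
- A reader might also infer a further loss because parents meet in groups of five. The document gives no intraclass correlation, and only the parents attend the groups, so it offers no basis for a clustering adjustment to the dyads. None is made here.

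**Conclusion.** The point holds as an internal inconsistency: the paragraph states a minimum of 18 dyads and forecasts a retention that yields 16. That rests on the document's own figures alone.

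The consequence is modest: about 0.05 SD in the detectable change at 80% power, or 4 to 6 percentage points of power, both under assumed power levels and a simple paired t test. The 21% chance of keeping 18 or more also assumes that dyads drop out independently. This is a minor to moderate correction to the sample-size statement. It does not call the design or the enrolment of 20 into question.

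**What to change.** - Make 20% attrition the base case: 16 of the 20 enrolled dyads are expected to remain. Quote the detectable change at that number, with the sponsor's own power stated. For a paired change at two-sided alpha 0.05 it is about 0.75 SD if the power is 80% and 0.87 SD if it is 90%.
- Delete the statement that 18 is a minimum, or reword it to say that 18 dyads remain only if attrition is 10% or less.
- Keep 0% (20 dyads) and 10% (18 dyads) as sensitivity scenarios.

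The cost is wording and a slightly less favourable headline figure (0.75 rather than 0.70 SD at 80% power). No extra families are needed. Only if the sponsor holds that 18 is a true requirement would enrolment have to change: 18/0.80 = 22.5, so 23 dyads, three more than planned.

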The UMMC is the state’s only academic medical center and has the only children’s hospital in the state. In 2019, 4464 AA children aged 8 to 11 years were treated by a UMMC pediatric clinic, and between November 2019 and April 2020, 170 AA children aged 8 to 11 years were identified with the risk for T2DM in the UMMC’s Prediabetes Registry. UMMC is a minority-serving, research-intensive health care organization with a state-mandated requirement to provide not less than 50% of their services to indigent persons (Mississippi Legal Code Annotated 37-115-27; 2017). The UMMC is also a national leader in telehealth [51] and has one of only 2 National Centers of Excellence in Telehealth in the nation [52]. The UMMC Center for Telehealth has successfully intervened with adults with uncontrolled T2DM [53] using remote patient monitoring and is piloting a similar single-arm feasibility trial with pediatric patients (10-17 years) [54]. Health systems with telehealth technology are encouraged to implement and evaluate weight loss interventions for patients at risk for T2DM [32,40,55], and Mississippi is at the forefront of advancing telehealth and adopting mandates for telehealth care reimbursement [51-53,56]. Thus, Mississippi is an ideal location to test the effectiveness and implementation of lifestyle interventions using telehealth in clinical care settings to treat obesity and prevent T2DM in AA youth at the highest risk for diabetes in the United States.

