### Data Analysis

Participant sociodemographic characteristics at baseline will be described using means and SDs, medians and ranges, or frequencies with percentages where applicable. The primary outcome evaluation will assess the change in child BMI *z* score (index participant) and parent BMI (coparticipant) from baseline to 12 and 30 weeks using repeated measures analysis of covariance with child Tanner stage as the covariate. Secondary analyses will include the comparison of anthropometric, biomarker, behavioral, psychosocial, and environmental measures adjusted for other factors. Generalized linear modeling will be used to assess the effect of the intervention, both unadjusted and adjusted (controlling for demographics, baseline BMI *z* score, and BMI). Data will be analyzed according to intention-to-treat principles [106-108].

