## Results

Recruitment and enrollment began in December 2020, and the first cohort of families will begin the intervention in March 2021. As of March 15, 2021, 10 children and their parents were enrolled in the study; however, intervention delivery had not begun. Future outcomes will be published in peer-reviewed health-related research journals and presented at national, regional, or state professional meetings and conferences. Preliminary findings will position the investigative team to design a subsequent hybrid study that will include a powered pilot randomized controlled trial with a larger sample of families and providers, a usual care control arm, and long-term follow-up; a robust evaluation of a refined implementation protocol; and cost-benefit and return-on-investment analyses.

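### A single arm of 16 to 20 dyads cannot supply the reliable effect size estimates promised for the next randomized trial

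*Protocol article*

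**What the plan says.** Participant Recruitment and Sample Size closes with an unqualified promise: "We will obtain reliable effect size estimates to design a pilot randomized controlled trial". The same paragraph sets the test, "Analyses are based on α=.05 and a conservative two-sided test", and a scale for judging effects, "An effect size of 1.0 is considered substantial and 0.5 is considered medium". It gives three analysable sample sizes: "assuming 10% attrition [37], a minimum of 18 dyads are needed", and "0% (n=20 dyads) and 20% (n=16 dyads) attrition". It then says that 20% attrition is anticipated, so 16 dyads is the plan's own expectation. It states no power level, no interval width and no precision target.

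The trial has one arm of 20 parent-child dyads, in four groups of five parents. Data Analysis nevertheless says: "Generalized linear modeling will be used to assess the effect of the intervention". Results describes the follow-on study as "a powered pilot randomized controlled trial with a larger sample of families and providers", with a usual care control arm.

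On background care, the documents pull in different directions. Families are recruited in the pediatric weight management clinic. Under Intervention Participant Retention, assessments coincide with the child's routine appointments there. Implementation Strategy describes the target families as referred to and engaged in intensive obesity treatment. The eligibility text, however, excludes families in which the child or parent is in a supervised weight loss program.

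**The concern.** A randomized trial against usual care is sized on the between-arm difference and the variability of the outcome. The promise implies that the pilot will supply that difference, and well enough to design on. An uncontrolled pre-post change is a different quantity, and at this sample size even the change itself is loosely estimated.

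Two things are at stake. If the next trial is sized on the observed change, its size could be badly wrong. And the pilot report may present as the effect of the intervention something that a single arm cannot isolate.

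**Working it through.** **Inputs.** From Participant Recruitment and Sample Size: two-sided α = .05; n = 16, 18 or 20 dyads; 0.5 is medium and 1.0 is substantial. Assumption: 80% power for the next trial, because the article states none.

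**1. The plan's own figures.** The retained counts reproduce: 20 × 0.9 = 18 and 20 × 0.8 = 16. The statement that 18 are needed cannot be reproduced, because no power is given and the five scenarios are not itemised. Working backwards with a paired t-test at 80% power, the detectable standardized change is 0.75 (n = 16), 0.70 (n = 18) and 0.66 (n = 20).

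**2. Width of the interval for the mean change.** Half-width in SD units = t(0.975, n−1)/√n.
- n = 16: 2.131/4 = 0.53
- n = 18: 2.110/4.243 = 0.50
- n = 20: 2.093/4.472 = 0.47

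**3. Interval for the standardized change.** The exact limits are the values δ at which the observed t = d√n lies at the 97.5th and 2.5th percentiles of a noncentral t with n−1 degrees of freedom and noncentrality δ√n.

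| Observed d | n = 16 | n = 18 | n = 20 |
|---|---|---|---|
| 0.5 | −0.03 to 1.01 | 0.00 to 0.98 | 0.03 to 0.96 |
| 1.0 | 0.38 to 1.59 | 0.42 to 1.56 | 0.45 to 1.53 |

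These treat families as independent. Similarity within the groups of five would widen them. With effective size 20/(1 + 4 × ICC) and an approximate standard error, the n = 20 interval around 0.5 becomes 0.02 to 0.98, −0.01 to 1.01 and −0.05 to 1.05 for assumed ICCs of 0.02, 0.05 and 0.10.

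**4. What this means for sizing a two-arm trial.** For the moment, read the standardized change as if it were a between-arm effect. A two-sample t-test at 80% power needs 64 per arm at 0.5 and 17 at 1.0. The normal approximation, 2(1.96 + 0.84)²/d², gives 63 and 16. For an observed 1.0 at n = 16, the same approximation at the interval's ends gives 15.7/0.38² ≈ 109 and 15.7/1.59² ≈ 6 per arm. For an observed 0.5 at n = 16 the lower limit is below zero, so no finite size follows from it.

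**5. The SD of change.** The 95% limits are the estimate times √[(n−1)/χ²]. At n = 16 these are √(15/27.49) = 0.74 and √(15/6.26) = 1.55. For a fixed target difference the required size varies with the square, so by a factor of 0.55 to 2.40. The SD is usable for planning, but only with allowance for its uncertainty.

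**6. The quantity estimated.** Pilot: mean at week 12 or 30 minus mean at baseline, in one arm. Next trial: difference between that change with the program and that change under usual care. The two agree only if the average change under usual care is zero. The pilot has no information on that change, and a larger sample would not supply it.

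**The case against.** **This is a pilot, and it says so.** The article speaks elsewhere of early efficacy and of preliminary findings, nowhere says that the next trial will be powered on the observed mean change, and calls that trial a pilot too. All of this is true, and it limits the harm. It does not qualify the sentence in the sample size section, which promises reliability outright. The small single-arm design is not at fault here; the property claimed for it is.

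**The value 0.5 is not the plan's assumption.** This is also fair: the article labels 0.5 as medium but does not plan on it. A reader might infer that 16 to 20 dyads always give an interval from no effect to substantial. The figures do not support that. The span is literal only at n = 16 with an observed 0.5; at n = 20 the interval narrowly excludes both ends, and an observed 1.0 excludes zero. What holds throughout is a half-width of about 0.5 SD.

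**The printed child SD of 0.05 implies good absolute precision**, 0.53 × 0.05 ≈ ±0.027 BMI z at n = 16, against a change of 0.1. That follows if the SD is right. But the same SD is printed for parent BMI, where it makes a change of 2.5 equal to 50 SDs, so it is weak support. Nor does it touch the missing comparator.

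**Concurrent clinic care is not settled.** This stands. Routine appointments and the reference to intensive obesity treatment suggest it. The exclusion of supervised weight loss programs points the other way, and the phrase about obesity treatment could mean the study program itself. These statements need reconciling. Time trends and regression to the mean remain in either case.

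**Direction of the error.** A reader might infer that a trial sized on the pilot change would be too small. The documents do not support that. It would require usual care to lower BMI z score, and the article gives no figure for this. Because stabilization counts as success, children might otherwise gain, in which case the pilot change would understate the effect against usual care.

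**Conclusion.** The promise of reliable effect size estimates is a stated property that the design does not have. The absence of a comparator is decisive at any sample size: the pilot estimates a within-group change, and the next trial tests a difference from usual care. The direction and size of the gap between them cannot be determined from the article.

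Imprecision adds to this. The half-width is 0.47 to 0.53 SD for 20 to 16 dyads, and at the anticipated n = 16 an observed medium change is compatible with none and with a substantial one. These figures rest on independent families and approximately normal changes; the trial sizes of 64 and 17 per arm also rest on an assumed 80% power.

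The conclusion concerns wording and the intended use of the results. It does not make the pilot unfit for its feasibility and implementation aims.

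**What to change.** In Participant Recruitment and Sample Size, replace the closing sentence with: *The pilot will give preliminary estimates, with 95% confidence intervals, of within-group change, the SD of change, the between-visit correlation and retention. The randomized trial will be sized on a separately justified target difference for child BMI z score and for parent BMI, using an upper confidence limit for the SD of change, not on the observed pilot change.*

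In Data Analysis, describe the modelled results as change during the program, not as the effect of the intervention.

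Reconcile the exclusion of supervised weight loss programs with the statements on routine clinic appointments and intensive obesity treatment, so that readers know what care accompanied the program.

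The cost is text edits and weaker efficacy language. No change to sample size, visits or data collection is needed.

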### Conceptual Model

Family Systems Theory, undergirded by family motivation and Social Learning Theory, and the Telehealth in Chronic Disease (TECH) model are the foundations for the TELE-GEN conceptual model (Figure 1). Social Learning Theory is used to guide intensive lifestyle interventions, such as the DPP [63]. The conceptual basis for the TELE-GEN intervention has evolved from pediatric obesity and T2DM prevention research using Family Systems Theory [64,65] and Social Learning Theory [66,67]. Successful Social Learning Theory–based intervention approaches include helping families make changes to the home food, physical activity, and screen time environment, increasing family motivation to make positive changes, and increasing family functioning around food, physical activity, and sedentary behaviors. These activities are thought to increase family efficacy for making lifestyle modifications and ultimately improving intervention outcomes. This theoretical approach is bolstered by applying the TECH model, which outlines effective pathways for the uptake of clinical telehealth interventions [68]. The TELE-GEN conceptual model is displayed in Figure 1.

**Figure 1 figure1:**
[figure not shown]
Telehealth diabetes prevention intervention and implementation conceptual model. DPP: Diabetes Prevention Program; PA: physical activity.

### Intervention

Power to Prevent [28] is a diabetes prevention intervention based on the DPP [63] and the *Small Steps, Big Rewards Program* [69] and is tailored for AA families. The goal of the program is to achieve a 5% to 7% weight loss by making modifications to dietary, physical activity, and sedentary behaviors. In the proposed pilot trial, modification to family dietary, physical activity (≥150 min per week), and sedentary behaviors will be targeted, in addition to individual-level parent behaviors. The *Power to Prevent*
*Leader Guide* and participant materials will be adapted and used in each session. The scientific literature strongly supports family-based approaches to treating youth with overweight or obesity [70]. Thus, group-based sessions (60 min) will be conducted with parents and target the adoption, maintenance, and self-regulation of family-focused dietary, physical activity, and sedentary behaviors. Parent participants will meet weekly for 11 weeks and then monthly for 4 pilot maintenance sessions (15 sessions in total; frequency and duration supported by the literature [71]). Sessions for all groups will be facilitated by a racially concordant lifestyle coach (interventionist) who will be trained in accordance with the Centers for Disease Control and Prevention Diabetes Prevention Recognition Program standards [72]. Wi-Fi–equipped iPads (12.9”) with cellular connectivity will be used to link families to videoconferencing sessions and to cooking and family-friendly physical activity video demonstrations via YouTube.

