### Participant Recruitment and Sample Size

In-person participant screening and enrollment will be conducted in the UMMC pediatric weight management clinic beginning in December 2020. Preliminary screening will the conducted by the clinical provider using a patient eligibility checklist that will screen for both child and parent eligibility. The lifestyle coach will immediately meet in the clinic room following the clinical encounter to conduct a full screening and provide detailed study information to interested parents and children. Consent forms will be verbally described to parents and children, and parent consent, parent permission, and child assent will be obtained before study enrollment.

Children will be eligible to participate if they are AA, overweight or obese (≥85th percentile for age- and sex-specific BMI), and aged between 8 and 11 years. The child age range was selected to allow for intervention occurring before the average age of youth-onset T2DM, 13 years [10]. The criteria for parents (biological, grandparent, or legal guardian) of eligible children included AA, overweight or obese (BMI ≥25 kg/m^2^), and coresidence with the child. Although mothers represent most participants in family-based studies, we will not use parents’ sex as an inclusion criterion. Parents and children must also be at risk for T2DM based on the following criteria: (1) parents’ T2DM risk will be assessed using the A1CNow^+^ system to measure point-of-care hemoglobin A_1c_ (HbA_1c_), which uses a drop of nonfasting blood (5.7%-6.4%), and the ADA prediabetes screening tool (score ≥5); (2) child risk will be based on the BMI percentile (≥85th percentile) and parents’ risk (BMI ≥25 and ADA screening or HbA_1c_).

Consistent with previous T2DM prevention interventions [26,57], we will exclude families if the child or parent has a history of T2DM or a screening HbA_1c_ level greater than 6.4%, is taking glucose-lowering medications, is participating in a supervised weight loss program, is pregnant or breastfeeding, has conditions limiting participation, has undergone weight loss surgery, or is moving out of state within 6 months. If a parent becomes pregnant during the study, we will include only child data (index participant) in the analyses. Technology literacy will not be included as an exclusion criterion. Participants will receive technology instruction from the telehealth center and be provided technical support as needed.

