#### Intervention Efficacy Measures

Primary and secondary outcome measures will be assessed at baseline (week 1), postintervention (week 12), and 4-month follow-up (week 30). The primary outcome measure will be a reduction or stabilization in the child BMI *z* score (index participant) and a reduction in parent BMI (coparticipant) [88]. Secondary outcomes include anthropometric (waist circumference and body composition), biomarker (HbA_1c_, blood pressure, resting heart rate, lipid profile, and Tanner stage), behavioral (fruit and vegetable, sugar-sweetened beverage, and sweat and salty snack consumption; family meal frequency; fast food meal frequency; physical activity volume; and sedentary time), psychosocial (self-efficacy, self-regulation, readiness to change, family functioning, and perceived stress), and environmental (home food and physical activity environment and perceived neighborhood support for healthy eating and physical activity) measures (Table 1). All the measurements will be recorded electronically using REDCap (Research Electronic Data Capture) tools hosted at the UMMC [89]. REDCap is a secure, web-based software platform designed to support data capture for research studies, providing an intuitive interface for validated data capture; audit trails for tracking data manipulation and export procedures; automated export procedures for seamless data downloads to common statistical packages; and procedures for data integration and interoperability with external sources.

**Table 1 table1:** Pilot trial outcome measures.

Outcome measure and instrument				Participant

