	**BMI**			
		Stature (0.1 cm) assessed using Seca stadiometer, and weight (0.1 kg) assessed using Tanita (TBF-400) body composition and weight scale; height and weight measured without shoes; BMI calculated using the CDC formula: weight (kg)/(height [m])^2^ [91]	Parent	

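### The parent planning effect of 2.5 BMI units is larger than the program's 5% to 7% weight-loss goal gives at any baseline BMI below 35.7, and the SD printed with it does not support it

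*Protocol article*

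**What the plan says.** The Intervention section of the protocol article sets a percentage target for the program: "The goal of the program is to achieve a 5% to 7% weight loss by making modifications to dietary, physical activity, and sedentary behaviors".

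The section on Participant Recruitment and Sample Size gives one parent effect in BMI units. The power calculation "shows detectable effect sizes, ≥−2.5 (SD 0.05) BMI in parents [58] and in children". The test settings follow: "Analyses are based on α=.05 and a conservative two-sided test". On numbers, "assuming 10% attrition [37], a minimum of 18 dyads are needed"; two further scenarios use 20 dyads (no attrition) and 16 dyads (20% attrition). No power level is printed. The same SD, 0.05, is printed for the child BMI z score. The paragraph labels a standardized effect of 1.0 substantial and 0.5 medium.

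The same section admits parents who are "overweight or obese (BMI ≥25 kg/m^2^), and coresidence with the child". It gives no upper BMI limit and no expected mean.

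Intervention Efficacy Measures defines the parent part of the primary outcome as "and a reduction in parent BMI (coparticipant"), assessed at baseline, week 12 and week 30. The efficacy Data Analysis section tests change from baseline. Neither section uses 2.5 as a threshold. Table 1 gives the BMI definition: "BMI calculated using the CDC formula: weight (kg)/(height [m])^2".

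**The concern.** The article prints two sizes for the parent effect, one as a percentage of weight and one in BMI units, and does not relate them. Over much of the eligible BMI range they disagree: the effect used for planning is larger than the loss the program sets out to achieve.

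This matters in two ways. First, a reader will take a figure called detectable as the smallest effect the trial can reliably see. If that were so, a group that met the program's goal could fall below it. If it is not so, the figure has no basis in the inputs printed beside it. Second, the paragraph says the pilot will supply effect sizes for designing a randomized trial. If 2.5 were carried forward as the reference effect for parents, that trial would be sized for more than the program aims to deliver, unless the parents are heavy enough.

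**Working it through.** **Inputs.** From the article: effect 2.5 (no unit printed; taken as kg/m²), SD 0.05, two-sided alpha 0.05, n = 16, 18 or 20, program goal 5% to 7%, entry from BMI 25. Assumed: adult height constant over 30 weeks; power 80%, with 90% as a check; a one-sample t-test on change from baseline as a simple stand-in for the planned repeated measures analysis of covariance.

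**Step 1: reproduce the plan's figures.** The attrition counts reproduce: 20 × 0.9 = 18 and 20 × 0.8 = 16. The detectable effect does not. The standardized detectable effect d is roughly (1.960 + 0.842)/√n at 80% power, which is 0.700, 0.660 and 0.626 for n = 16, 18 and 20. The noncentral t distribution gives slightly larger values, used below.

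| n | d at 80% power | Detectable change if SD = 0.05 (d × 0.05) | SD of change at which 2.5 is detectable (2.5/d) |
|---|---|---|---|
| 16 | 0.749 | 0.038 | 3.34 |
| 18 | 0.701 | 0.035 | 3.57 |
| 20 | 0.660 | 0.033 | 3.79 |

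At 90% power the last column becomes 2.88, 3.08 and 3.27. With the printed SD, the standardized effect would be 2.5/0.05 = 50, against the article's own label of 1.0 as substantial.

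**Step 2: put the goal and the planning effect on one scale.** BMI is weight divided by height squared. With height fixed, a loss of p% of weight is a loss of p% of BMI, so BMI fall = p × baseline BMI.

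| Baseline BMI | Fall at 5% loss | Fall at 7% loss | 2.5 as % of baseline |
|---|---|---|---|
| 25 | 1.25 | 1.75 | 10.0 |
| 30 | 1.50 | 2.10 | 8.3 |
| 35 | 1.75 | 2.45 | 7.1 |
| 40 | 2.00 | 2.80 | 6.3 |

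The baseline BMI at which the two agree is 2.5/p: 2.5/0.07 = 35.7, 2.5/0.06 = 41.7 and 2.5/0.05 = 50. At BMI 30, 2.5 is 2.5/2.10 = 1.19 to 2.5/1.50 = 1.67 times the goal.

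**Step 3: what it means for power.** This depends on the SD of change. The table gives power at n = 18 for the goal-level falls at BMI 30. All SDs other than 0.05 are assumptions.

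| SD of change | Power for a fall of 1.5 | Power for a fall of 2.1 |
|---|---|---|
| 0.05 (printed) | >99.9% | >99.9% |
| 2 | 85% | 99% |
| 3 | 52% | 80% |
| 3.5 | 40% | 67% |

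An SD that makes 2.5 the detectable effect at 80% power (about 3.6 at n = 18) therefore leaves a goal-level fall at BMI 30 with roughly 40% to 67% power or slightly less. With an SD well below that, the detectable change would be well below 2.5.

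**Step 4: effect on a later trial, if 2.5 were carried forward.** For a fixed SD, the required sample size varies with 1/effect². If the true effect were 2.10 or 1.50, the trial would need (2.5/2.10)² = 1.4 or (2.5/1.50)² = 2.8 times the number planned on 2.5.

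**The case against.** The strongest reply is that a program goal and a detectable effect answer different questions and need not be equal. The 5% to 7% describes the source program; for the pilot, the Intervention section goes on to name behaviours rather than a weight loss. The printed figure is also ambiguous: it has no unit, and read literally the inequality includes smaller falls. The article condenses five scenarios whose results are not shown, and the source cited for the figure is not available here. All of this stands as a reason for caution. It does not explain why the only parent effect in BMI units exceeds the program's goal at common eligible BMIs, nor why an SD of 0.05 accompanies it.

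A reader might go further and infer three things the document does not support.

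- That a parent group meeting the goal would fail the primary endpoint. It would not. The outcome is a reduction in BMI tested against baseline, with no 2.5 threshold, and a 5% to 7% loss is a reduction at any starting BMI.
- That the trial is underpowered for a goal-level loss. At the printed SD, power exceeds 99.9%. A shortfall appears only with an assumed SD of change of about 2.5 to 3.5 or more, which the article does not give.
- That the trial could not tell whether the program met its goal. Weight is measured to 0.1 kg and the outcomes are assessed at all three visits, so percent loss can be computed.

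Nor can it be said that the group mean must fall short of 2.5. Mean baseline BMI is not given, and above 35.7 a 7% loss reaches it.

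**Conclusion.** The point holds as a fault in the planning statement, not in the endpoint. The 2.5-unit parent effect is optimistic relative to the program's own goal for every parent below BMI 35.7 even if the top of the goal is reached, and for every parent below BMI 50 if only the bottom is reached. At BMI 30 it is 1.2 to 1.7 times the goal. The SD of 0.05 does not support it as a detectable effect. That SD implies a detectable change of about 0.035 at n = 18, whereas 2.5 would need an SD of change of about 3.3 to 3.8 across n = 16 to 20.

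The comparison of goal and effect rests on fixed adult height and on reading 2.5 as kg/m². The SD figures rest also on an assumed 80% power and a one-sample test of change. How far the enrolled group is affected depends on its mean BMI and on the true SD of change, neither of which is in the article.

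**What to change.** In Participant Recruitment and Sample Size, do one of two things.

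- Restate the parent planning effect as the BMI change that 5% to 7% implies at the expected mean baseline BMI. Give a realistic SD of change, its source, and the resulting power or confidence-interval width at n = 16 to 20.
- Or state that 2.5 exceeds the program goal and is not a reference for success. The SD printed beside it still needs correcting.

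Keep parent BMI change as the primary outcome. Replacing it with percent weight change is not advised, since 10 families were already enrolled by March 15, 2021. Instead, add a supporting analysis: percent weight change from baseline, and the number of parents losing at least 5%, at weeks 12 and 30. This shows directly whether the program met its goal and does not depend on how heavy the parents are. In absolute BMI, the same 6% loss counts as 0.06 × 40 = 2.4 at BMI 40 but 0.06 × 25 = 1.5 at BMI 25.

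The cost is a smaller, less favourable stated effect and a little more analysis. No new data are needed.
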